## Abstract

**Background:**

The incidence of cardiovascular disease (CVD) in rheumatoid arthritis (RA) is increased compared to the general population. Immune dysregulation and systemic inflammation are thought to be associated with this increased risk. Early diagnosis with immediate treatment and tight control of RA forms a central treatment paradigm. It remains unclear, however, whether using tumor necrosis factor inhibitors (TNFi) to achieve remission confer additional beneficial effects over standard therapy, especially on the development of CVD.

**Methods/Design:**

Coronary Artery Disease Evaluation in Rheumatoid Arthritis (CADERA) is a prospective cardiovascular imaging study that bolts onto an existing single-centre, randomized controlled trial, VEDERA (Very Early versus Delayed Etanercept in Rheumatoid Arthritis). VEDERA will recruit 120 patients with early, treatment-naïve RA, randomized to TNFi therapy etanercept (ETN) combined with methotrexate (MTX), or therapy with MTX with or without additional synthetic disease modifying anti-rheumatic drugs with escalation to ETN following a ‘treat-to-target’ regimen. VEDERA patients will be recruited into CADERA and undergo cardiac magnetic resonance (CMR) assessment with; cine imaging, rest/stress adenosine perfusion, tissue-tagging, aortic distensibility, T1 mapping and late gadolinium imaging. Primary objectives are to detect the prevalence and change of cardiovascular abnormalities by CMR between TNFi and standard therapy over a 12-month period. All patients will enter an inflammatory arthritis registry for long-term follow-up.

**Discussion:**

CADERA is a multi-parametric study describing cardiovascular abnormalities in early, treatment-naïve RA patients, with assessment of changes at one year between early biological therapy and conventional therapy.

**Trials registration:**

This trial was registered with Current Controlled Trials (registration number: ISRCTN50167738) on 8 November 2013.

## Background

Rheumatoid arthritis (RA) is one of the most common autoimmune diseases affecting approximately 1% of the population in the United Kingdom [1]. RA is a chronic, systemic inflammatory arthritis and, if not adequately controlled, can lead to significant joint damage and subsequent functional impairment. Mortality is increased up to three-fold compared to the general population, largely due to increased frequency of premature cardiovascular disease (CVD), which causes up to 40% of mortality cases in RA patients [2], and is as high as that of patients with other major CVD risk factors such as type 2 diabetes mellitus [3]. It is accepted that CVD risk in RA is independent of, and incremental to, traditional CVD risk factors [4], with the likely predominant pathological process being immune dysregulation leading to systemic inflammation [5], however the exact mechanisms remain unclear. The inflammatory process, mediated through pro-inflammatory cytokines such as tumor necrosis factor (TNF), is linked to atherosclerosis and plaque rupture and has confounding effects on lipid and glucose metabolism, blood pressure and hemostatic factors [6]. Markers of RA severity are strongly associated with adverse cardiovascular (CV) outcomes in RA [7], with atherosclerosis itself being increasingly viewed as an inflammatory-mediated process [8].

Arterial stiffness is associated with an increased risk of CV events with a range of co-morbidities [9]. In patients with RA without traditional CV risk factors, aortic pulse wave velocity is higher than in controls [10] and correlates with age, mean arterial pressure and C-reactive protein (CRP). Echocardiography studies have shown that patients with RA have high rates of diastolic dysfunction [11], heart failure [12, 13] and heart failure with preserved ejection fraction (EF) [14]. Positron emission tomography (PET) in patients with rheumatic diseases without coronary artery disease (CAD) shows lower myocardial blood flow (MBF) reserve compared to controls, with an inverse correlation to disease duration [15]. In a meta-analysis of 22 studies, RA patients had a greater carotid intimal-media thickness ((CIMT) a direct measure of the status of the vascular wall and measure of atherosclerotic and arteriosclerotic processes [16]) than controls [17], with emerging evidence that CIMT is abnormal even in early disease [18]. These findings are consistent with the concept of microvascular pathology and accelerated atherosclerosis due to systemic inflammation in RA, which may precede and contribute to the effects of CAD.

Early diagnosis of RA and immediate intervention with conventional disease modifying anti-rheumatic drugs (DMARDs) in a treat-to-target approach, with remission the goal of treatment, is an internationally recommended, established practice [19]. Biological DMARD (bDMARD) treatments, first introduced at the turn of the century, are highly effective tools to achieve this and have revolutionized outcomes in RA. The TNF-inhibitors (TNFi) were the first bDMARD agents to be introduced, applied in the methotrexate (MTX) failure population, with remarkable structural benefits also observed. More recently however, first-line TNFi studies in early RA have demonstrated particularly high rates of remission induction, similar or slightly greater than conventional DMARD, but with superior structural benefits and the ability to achieve drug-free remission [20–26]. In addition, reports have suggested wider benefits of bDMARD therapy including reduction in biomarkers associated with CVD [27, 28]. Recent pilot data has shown that tocilizumab treatment for over one year significantly increased left ventricular ejection fraction and decreased left ventricular mass index associated with disease activity [29].

CV clinical trials of TNFi treatments in RA are challenging because of the small number of hard clinical CV mortality endpoints in study populations [30], and being unable to adjust for important confounders that differentiate between CV events that follow other pathophysiological pathways [31]. As TNFi treatment is reserved for patients with established, MTX-resistant diseases, observational studies are inherently limited by a selection bias. Although aggressive treat-to-target approaches with conventional DMARDs are associated with impressive remission rates, the use of bDMARD may offer a ‘window of opportunity’ in early RA by interrupting progression along the disease continuum, and consequently may have the additional potential to impact CVD.

### Detection of cardiovascular disease in rheumatoid arthritis

The imaging modalities currently used for the assessment of CVD in RA are transthoracic echocardiography (TTE), single-photon emission computed tomography (SPECT) and cardiovascular magnetic resonance (CMR) [32]. PET is recognized as the gold standard for MBF quantification but is hindered by high cost and low availability and offers little functional information. SPECT is commonly used for ischemia testing but, as with PET, it cannot assess cardiac structure and exposes patients to a significant dose of ionizing radiation [33]. TTE is a safe, low-cost examination that can assess cardiac structure and function and provides information on ischemia and viability when combined with exercise and/or pharmacological stress. Poor acoustic windows can be a common problem due to obesity or acoustic shadowing from the lungs and reporting variability limits its reproducibility.

### Cardiovascular magnetic resonance

CMR is widely recognized as a safe, sensitive, reproducible and comprehensive non-invasive imaging test to detect CVD. Both anatomical and functional assessment can be made with CMR. Left ventricular (LV) mass and function can be measured more accurately than with any other imaging method [34]. Aortic distensibility can be reliably measured from the ascending or descending aorta [35]. Tissue tagging provides measurements of regional and global myocardial strain as an early marker of contractile dysfunction [36]. We have shown in a large study of patients with suspected angina that CMR can detect myocardial ischemia with greater sensitivity than nuclear perfusion imaging [37]. Dynamic contrast enhanced CMR methods combined with quantitative analysis can be used to estimate MBF at rest and during hyperemic stress [38]. Perfusion CMR has demonstrated reduced MBF reserve in asymptomatic adults with CVD risk factors, suggesting it can detect preclinical pathology [39]. T1 mapping methods are used to measure the extent of the extracellular matrix in the heart, which expands in response to inflammation and fibrosis [40]. CMR has no harmful effects and multiple measurements can be combined in a single imaging protocol [35].

The literature on CMR in RA is sparse. In contrast to previous TTE studies, CMR shows that patients with RA have reduced LV mass and EF [41]. No previous studies have combined macrovascular, microvascular and detailed myocardial assessment by CMR in RA, such that the full potential of CMR for a comprehensive multi-parametric and quantitative evaluation of CVD in RA has not yet been realized.

### Hypotheses

We hypothesize that the CADERA study will determine, using multi-parametric CMR, that i) subclinical CV pathology exists in patients with early, treatment-naïve RA, ii) early aggressive control of RA can reduce this subclinical CV pathology at one year from treatment initiation and iii) TNFi offer additional benefit over and above conventional DMARD in the burden of subclinical CV pathology.

## Methods/Design

### Study design

CADERA bolts on to the VEDERA (Very Early versus Delayed Etanercept in Rheumatoid Arthritis) trial, a prospective longitudinal intervention study of patients with early RA, randomized to either first-line TNFi therapy (etanercept, ETN) and MTX or optimal synthetic DMARD therapy. VEDERA is an investigator-initiated research (IIR) study based at the Leeds Institute of Rheumatic and Musculoskeletal Medicine, and is funded by an unrestricted educational grant that is part of an IIR agreement with Pfizer. VEDERA is a phase IV, single-centre study of 120 patients with new-onset, treatment-naïve RA, randomized to either immediate ETN and MTX combination or initial MTX and a treat-to-target regimen (optimal, standard conventional therapy approach); with step-up in the latter group to ETN and MTX combination therapy in patients failing to achieve a pre-defined target of remission after 24 weeks. The aim of VEDERA is to assess for the depth of remission (clinical and imaging) and immunological normalization induced by the treatment arms, as well as to identify predictors of remission.VEDERA patients will be recruited to CADERA and undergo CMR at baseline (prior to treatment) as well as after one and two years of treatment (see Figure 1). The change in CVD status as defined by CMR between baseline and follow-up in patients treated with early biological or optimal DMARD therapy will be determined. The study flow chart is presented in Figure 1. At the end of the study all patients will enter an inflammatory arthritis registry based at the National Institute for Health Research (NIHR) Leeds Musculoskeletal Biomedical Research Unit (LMBRU).

**Figure 1 Fig1:**
[figure not shown]
**Coronary Artery Disease Evaluation in Rheumatoid Arthritis (CADERA) study flow diagram.** *Etanercept non-responders or intolerance managed at physician’s discretion. ^#^Methotrexate for duration of study, addition of other DMARDs at week eight if not in remission and escalated to etanercept at week 24 if not in remission. ^~^Etanercept discontinued at the primary endpoint unless clinically indicated and at physician’s discretion. DAS, disease activity score; DMARD, disease modifying anti-rheumatic drug; HRUS, high-resolution ultrasound; LTHT, Leeds Teaching Hospitals NHS Trust; MCP, metacarpophalangeal; RA, rheumatoid arthritis; TT, treat-to-target; VEDERA, Very Early versus Delayed Etanercept in Rheumatoid Arthritis.

The National Research Ethics Service Committee Yorkshire and The Humber - Leeds West has approved the study protocol and other relevant documentation (Research Ethics Committee reference: 10/H1307/138).

### Enrolment criteria

Patients eligible for VEDERA will be recruited from the Leeds Teaching Hospitals NHS Trust Rheumatology service. The recruitment period is expected to last up to 36 months. All patients recruited to VEDERA will be offered inclusion to the CADERA study. CADERA CMR scans will be performed and analyzed at Leeds General Infirmary. The study will be performed in accordance with the Declaration of Helsinki (October 2000), with all patients providing informed written consent.

Inclusion criteria for VEDERA, and therefore CADERA, are patients diagnosed with RA according to the 2010 American College of Rheumatology/The European League Against Rheumatism (ACR/EULAR) criteria (Table 1), who have not yet received therapy with DMARDs, have early (symptoms for less than one year) active disease (clinical or imaging evidence of synovitis and Disease Activity Score in 28 joints with Erythrocyte Sedimentation Rate (DAS28-ESR) ≥3.2) and at least one poor prognostic factor (anti-citrullinated peptide antibody (ACPA) +/- abnormal power doppler in at least one joint).

**Table 1 Tab1:** **The 2010 ACR/EULAR classification criteria for rheumatoid arthritis**

Criteria	Score
Joint distribution	
1 large joint	0
2-10 large joints	1
1-3 small joints (large joints not counted)	2
4-10 small joints (large joints not counted)	3
>10 joints (at least one small joint)	5
Serology	
Negative RF AND negative ACPA	0
Low positive RF OR low positive ACPA	2
High positive RF OR high positive ACPA	3
Symptom duration	
<6 weeks	0
≥6 weeks	1
Acute phase reactants	
Normal CRP AND normal ESR	0
Abnormal CRP OR abnormal ESR	1

A score of six or more equates to definite RA. This requires that the patient has at least one joint with definite synovitis and that the synovitis is not better explained by another disease. The score may be retrospective or prospective. ACPA, anti-citrullinated peptide antibody; CRP, C-reactive protein; ESR, erythrocyte sedimentation rate; RF, rheumatoid factor.

Exclusion criteria are previous treatment with DMARDs, known CVD, contraindications to TNFi therapy (or severe co-morbidity that would in the clinician’s opinion be associated with unacceptable risk of receiving TNFi therapy) and contraindications to CMR, (which include renal failure (estimated Glomerular Filtration Rate (eGFR) <30 ml/min/1.73 m^2^), known allergy to gadolinium-based contrast agents and contraindications to adenosine (asthma or high-grade heart block)).

### Primary outcome measure

The primary outcome measure is aortic distensibility. It will be measured and quantified at baseline and at one year in each arm of the study. Increased arterial stiffness is associated with an increased risk of CV events [9]. It can be measured by pulse wave velocity or as distensibility of the aorta, but requires careful correction for age and blood pressure. It has previously been shown that aortic distensibility relates to clinical outcome and that TNFi improve aortic distensibility [27]. We performed a pilot study in 10 patients with RA (disease duration 20 ± 9.6 years) and matched by age and gender to 10 asymptomatic subjects without RA. Aortic distensibility was significantly different in RA patients, with a mean and standard deviation of 1.83 ± 0.4 cm^2^ versus 2.6 ± 0.6 cm^2^ in controls. LV volumes and mass were similar between groups and LV strain and twist showed trends towards a reduction in RA patients, but without reaching statistical significance. Our pilot data therefore suggested CV abnormalities in patients with RA in several quantitative CMR parameters, with aortic distensibility reaching statistically significant difference even in the small sample size.

Longitudinal changes of outcome measures in response to therapy will be measured and compared between the two treatment arms at baseline, one and two year time points. Secondary outcome measures are i) myocardial perfusion reserve, ii) LV strain and twist, iii) LVEF and iv) LV mass. Exploratory outcome measures are pre- and post-contrast T1 mapping, extra-cellular volume (ECV) and biomarker measurements.

Significant differences (expressed as *P* <0.05) of CV abnormalities detected by CMR between the two treatment arms will be presented, and the magnitude of this difference will be expressed as a 95% confidence interval.

### Sample size calculation

Power calculations are based on a previous study by Ikonomidis *et al*. [28]. We assumed an effect size of 2.46 cm^2^dyne^-1^10^-6^, representing 75% of the difference between treated (Anakinra) and non-treated RA patients reported by Ikonomidis *et al*. [28]. Mean aortic distensibility at baseline to post-treatment for treated and non-treated patients was 1.56 cm^2^dyne^-1^10^-6^ and 4.6 cm^2^dyne^-1^10^-6^, respectively. The standard deviation (SD) of the post-treatment measurements in the Anakinra group was 3.2 cm^2^dyne^-1^10^-6^ and a more conservative estimate of 3.5 cm^2^dyne^-1^10^-6^ has been used in the CADERA power calculation. Assuming an SD of 3.5 cm^2^dyne^-1^10^-6^, a power of 70%, 80% and 90% would be achieved at 5% significance level in a two-tailed independent samples Student’s t-test with 26, 33 and 44 patients respectively in the primary outcome measure of aortic distensibility in each treatment group (30, 38 and 50 when adjusted for 10% dropout).

Both treatment arms will be compared with primary outcome aortic distensibility from baseline to one-year follow-up, as well as other outcome measures. Analysis will be conducted in the R environment for statistical computing (R Core Team, 2012. R: A language and environment for statistical computing. R Foundation for Statistical Computing, Vienna, Austria). Exploratory data analysis will be used to determine if parametric (independent samples Student’s t-test) or non-parametric (Wilcoxon rank sum test) analyses are appropriate, and to summarize the distribution of aortic distensibility and change in other outcome measures across the two treatment arms. These analyses will also allow the credibility of an equal variance assumption to be assessed in parametric modeling and to be appropriately modeled [42]. All patients meeting eligibility criteria will be included in the analyses and these will be conducted at the end of the recruitment period. Exploratory subgroup analyses will be conducted separately by other comorbidities, a maximum of two to three that are clinically plausible, with appropriate correction for multiple testing [43]. Interactions between subgroups and interactions between CMR findings and biomarkers will be explored through building a linear model with interaction terms [44]. Patterns of CVD pathology in RA patients will be described. Treatment effects on secondary outcome measures and effects at the two-year follow-up point will be analyzed in an equivalent manner.

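### The planning effect of 2.46 is not 75% of the difference between the two means quoted for it (that would be 2.28), so the basis of the power statement must be reconciled

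*Protocol article*

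**What the plan says.** All the design inputs are in the protocol article, under Sample size calculation.

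- Effect: "We assumed an effect size of 2.46 cm^2^dyne^-1^10^-6^, representing 75% of the difference between treated (Anakinra) and non-treated RA patients".
- Source means: "Mean aortic distensibility at baseline to post-treatment for treated and non-treated patients was 1.56 cm^2^dyne^-1^10^-6^ and 4.6 cm^2^dyne^-1^10^-6^, respectively".
- Variability: the source SD is given as 3.2, and "a more conservative estimate of 3.5 cm^2^dyne^-1^10^-6^ has been used in the CADERA power calculation".
- Test and power: "a power of 70%, 80% and 90% would be achieved at 5% significance level" in a two-tailed independent-samples t-test.
- Sizes: "26, 33 and 44 patients respectively in the primary outcome measure of aortic distensibility in each treatment group", becoming "30, 38 and 50 when adjusted for 10% dropout".

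Under Primary outcome measure, the article reports that distensibility was lower in RA patients than in controls in its pilot (1.83 against 2.6). It also says that TNF inhibitors improve distensibility. A higher value is therefore the better one.

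**The concern.** The effect is defined as a fixed share of a difference, and the two means that form this difference stand in the next sentence. They do not give the effect that was used. Every listed sample size rests on that effect, and this is the article's only power statement for its primary outcome.

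The order of the means is also odd. Read literally, treated patients have 1.56 and non-treated patients 4.6, so the study cited to support a benefit would show the treated group worse.

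At stake is whether a reader can rely on the 70%, 80% and 90%. If the effect was meant to be 2.28, those figures are too favourable, and the allowance for dropout is largely absorbed.

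**Working it through.** **Inputs** (protocol article, Sample size calculation): effect 2.46; stated share 75%; means 1.56 and 4.6; SD 3.5 (source SD 3.2); two-sided alpha 0.05; two-sample t-test; 26, 33 and 44 per arm; 10% dropout. Equal allocation is assumed, since one size is given for each group. Effects, means and SDs are in the article's distensibility units.

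**1. Reproducing the plan's own figures.** With d = effect/SD, the power is that of a two-sided t-test with 2n − 2 degrees of freedom and noncentrality d × √(n/2). For 2.46 and 3.5, d = 0.703. The sizes for 70%, 80% and 90% power are 25.98, 32.76 and 43.52, which round up to 26, 33 and 44. These match the article exactly. The power at those sizes is 70.0%, 80.3% and 90.3%. Dividing by 0.9 for dropout gives 29, 37 and 49, one below the article's 30, 38 and 50 in each case, which is immaterial.

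**2. Checking the effect against its stated definition.**

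- Difference of the quoted means: 4.6 − 1.56 = 3.04.
- 75% of it: 0.75 × 3.04 = 2.28.
- Share that 2.46 represents: 2.46 / 3.04 = 80.9%.
- Difference for which 2.46 is 75%: 2.46 / 0.75 = 3.28.

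Rounding does not explain the gap. With the means anywhere in 1.555 to 1.565 and 4.55 to 4.65, the 75% figure runs from 0.75 × (4.55 − 1.565) = 2.24 to 0.75 × (4.65 − 1.555) = 2.32.

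Reading the two values as changes from baseline does not help either. With the same sign the difference is still 3.04. With opposite signs it is 6.16, and 75% of that is 4.62.

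**3. What follows if 2.28 was intended (SD 3.5, d = 0.651).**

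| Stated power | n per arm | Noncentrality at 2.46 | Power at 2.46 | Noncentrality at 2.28 | Power at 2.28 |
|---|---|---|---|---|---|
| 70% | 26 | 2.53 | 70.0% | 2.35 | 63.4% |
| 80% | 33 | 2.86 | 80.3% | 2.65 | 74.1% |
| 90% | 44 | 3.30 | 90.3% | 3.06 | 85.6% |

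The sizes for 70%, 80% and 90% at 2.28 are 30.08, 37.98 and 50.50, so 31, 38 and 51 evaluable per arm. Dividing by 0.9 gives 35, 43 and 57. The article's dropout-adjusted 30, 38 and 50 would then be about the evaluable number required, leaving almost nothing for dropout. The 90% option would rise from 2 × 50 = 100 to 2 × 57 = 114 of the 120 parent-trial patients.

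**4. Sensitivity to the SD.** With 2.28 and the source SD of 3.2 (d = 0.713), power at 26, 33 and 44 per arm is 71.2%, 81.3% and 91.1%.

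**5. The sample that might be available.** Assuming that all 120 parent-trial patients join in equal arms, 60 × 0.9 = 54 per arm are evaluable, and power at 2.28 with SD 3.5 is 91.8%. With 50 evaluable per arm it is 89.7%.

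**The case against.** The strongest reply is that the design inputs, 2.46 and 3.5, are explicit and give exactly the stated sizes. On this view the fault may lie in one descriptive sentence about an outside study: a misprinted mean, or a percentage that should read about 81%. The power figures would then stand. This is correct. A reader might infer that every stated power is overstated, but the article does not support that. It would require the means and the 75% rule both to be right and 2.46 to be the error, and nothing in the text settles this.

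A reader might also infer that the two group labels have simply been swapped. That is likely, given the direction of benefit described under Primary outcome measure, but it is not proven. The sentence is garbled (it speaks of baseline to post-treatment), and a wrong value is another possibility. Label order has no bearing on power in any case, because a two-sided test uses the size of the difference and not its sign.

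A further reply is that the SD was deliberately raised from 3.2 to 3.5. At 3.2, an effect of 2.28 still gives the stated powers. That also stands: what would be lost is the safety margin built into the SD. The article chose 3.5 as its planning value, however, so its power statement should hold at 3.5.

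None of these replies removes the contradiction between the effect, the percentage and the means.

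**Conclusion.** The sample size section is internally inconsistent. An effect of 2.46 is not 75% of the difference between 1.56 and 4.6, and neither rounding nor another reading of the two values yields it. The printed order of the means also conflicts with the expected direction of benefit, so a label or a value is probably wrong.

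The effect on power is conditional. If 2.46 is right, the stated figures are correct. If the means and the 75% rule are right and the SD is 3.5, each figure is too high by about 4 to 7 percentage points.

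Severity is moderate. The article lists three options and commits to no single target size or power. The trial is not shown to be underpowered: near-full uptake in equal arms would give about 92% even at 2.28. Uptake is an assumption here, since the article says only that parent-trial patients will be offered the imaging study.

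**What to change.** Check four items against the cited study: the effect, the percentage, the two means, and which group each mean belongs to. Also state whether the means are post-treatment values or changes from baseline. Then:

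- If 2.28 is the intended effect, replace 2.46 and restate power as about 63%, 74% and 86% at 26, 33 and 44 per arm. It may be noted that 70%, 80% and 90% would correspond to 31, 38 and 51 evaluable per arm, or 35, 43 and 57 with 10% dropout.
- If 2.46 is right, correct the means so that they differ by 3.28, or correct the percentage to about 81%, and leave the power figures as they are.
- In either case, correct the labels if the source shows that they are swapped.

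The cost is one check of a citation and a short correction. No extra enrolment is required, and the only possible loss is a less favourable stated power.

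### Power rests on a single-visit SD while the comparison is worded as change from baseline; if change is tested, the SD of 3.5 is not shown to be conservative

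*Protocol article*

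**What the plan says.** All the planning inputs are in the protocol article under Sample size calculation.

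- **Effect.** "We assumed an effect size of 2.46" (in 10^-6 cm²/dyne), described as "representing 75% of the difference between treated (Anakinra) and non-treated RA patients" in a cited anakinra study.
- **Source means.** "Mean aortic distensibility at baseline to post-treatment for treated and non-treated patients was 1.56" and 4.6 respectively. The wording spans baseline to post-treatment, which reads most naturally as mean change.
- **SD.** "The standard deviation (SD) of the post-treatment measurements in the Anakinra group was 3.2". The calculation uses 3.5 and calls it the more conservative choice.
- **Power.** For 26, 33 and 44 patients per arm, the article states that "a power of 70%, 80% and 90% would be achieved". The test is an unpaired t-test at the two-sided 5% level.
- **Planned comparison.** "Both treatment arms will be compared with primary outcome aortic distensibility from baseline to one-year follow-up", by t-test or Wilcoxon rank sum test, with no baseline term mentioned for the primary comparison.

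The Abstract, Study design and Primary outcome measure sections also describe the aim as comparing change over time between the arms. No section gives an SD of change or a correlation between baseline and one-year distensibility.

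**The concern.** A difference between arms in mean change has to be judged against the spread of individual changes. The spread of values at one visit is a different quantity. The two coincide only at one particular baseline to follow-up correlation. Raising 3.2 to 3.5 allows for uncertainty in a single-visit SD, but it does not turn that SD into an SD of change. If change is what will be tested, the three published power figures depend on a correlation that the article does not state.

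What is at stake is how the result is read. If distensibility tracks only modestly over a year and change is tested, the trial has less power than stated, and a null result would be given too much weight.

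**Working it through.** **Inputs from the article:** effect 2.46; single-visit SD 3.2 as reported and 3.5 as planned; two-sided 5% independent-samples t-test; 26, 33 and 44 per arm.

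**Assumptions:** equal SD s at both visits; correlation r between baseline and one year, not given, so shown as a range. The effect of 2.46 is taken as stated.

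**1. Reproduce the stated figures.** Standardised effect = 2.46/3.5 = 0.703. The noncentral t calculation gives 25.98, 32.76 and 43.52 per arm for 70%, 80% and 90% power, which round up to 26, 33 and 44. The calculation therefore applies 3.5 directly as the SD of whatever quantity is tested.

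**2. SD of change.** SD(change) = s × √(2(1 − r)).

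**3. Correlation needed for the stated power.** SD(change) ≤ 3.5 requires r ≥ 1 − 3.5²/(2s²).
- s = 3.5: r ≥ 1 − 12.25/24.50 = 0.50.
- s = 3.2: r ≥ 1 − 12.25/20.48 = 0.40.

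**4. Power across r, single-visit SD 3.5.** For ANCOVA of the one-year value on arm and baseline, the residual SD is 3.5 × √(1 − r²). The single degree of freedom spent on the covariate is ignored.

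| r | SD of change | Power on change at 26 / 33 / 44 per arm | n per arm for 80% on change | ANCOVA residual SD | ANCOVA power at 33 per arm |
|---|---|---|---|---|---|
| 0.2 | 4.43 | 50 / 60 / 73% | 52 | 3.43 | 82% |
| 0.3 | 4.14 | 56 / 66 / 79% | 46 | 3.34 | 84% |
| 0.4 | 3.83 | 62 / 73 / 85% | 40 | 3.21 | 87% |
| 0.5 | 3.50 | 70 / 80 / 90% | 33 | 3.03 | 90% |
| 0.6 | 3.13 | 79 / 88 / 95% | 27 | 2.80 | 94% |
| 0.7 | 2.71 | 89 / 95 / 99% | 21 | 2.50 | 98% |

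**5. Same check with the reported SD of 3.2.** Power on change at 33 per arm is 68% (r = 0.2), 74% (0.3), 80% (0.4), 87% (0.5), 93% (0.6) and 98% (0.7).

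**6. If one-year values are tested instead.** Under randomisation the expected difference between arms at one year equals the expected difference in change. The relevant SD is then the single-visit SD, and with 3.5 the power is 70%, 80% and 90% whatever r is.

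**The case against.** The strongest reply is that the article does not tie the t-test to change scores. It names the primary outcome simply as aortic distensibility, and in the analysis paragraph the word change is attached to the other outcome measures. A t-test on one-year values fits that text, and for it a single-visit SD is the right input. The sentence giving the source means is also hard to trust. Read literally as changes, and in the order given, it has untreated patients improving by 4.6 and treated patients by 1.56. Only the cited study could settle whether these figures are values or changes. This part of the objection stands: the mismatch is conditional on what is analysed.

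Two further points also stand in part. The margin from 3.2 to 3.5 does some work, since with a true single-visit SD of 3.2 it covers correlations from about 0.40 upwards. And the article does not commit to 33 per arm. All patients in the parent trial of 120 are to be offered entry. Assuming full uptake, 1:1 allocation and 10% dropout, 54 per arm remain, with power on change of 82% at r = 0.2 and 86% at r = 0.3 (SD 3.5). Uptake is not stated, so this softens the consequence without making the powers quoted at 26, 33 and 44 correct for change.

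A reader might infer that the trial is underpowered, or that the SD is simply wrong. The document supports neither. The correlation is unknown, and above the threshold the plan has more power than it claims.

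**Conclusion.** The point holds as an unsupported planning SD together with an analysed quantity that is not fixed. It is not a demonstrated loss of power. If change is tested without adjustment, the stated powers need r of at least about 0.5 (single-visit SD 3.5) or about 0.4 (single-visit SD 3.2), and describing 3.5 as conservative is not justified. If one-year values are tested, the stated powers stand for the assumed effect and SD. The practical size of the ambiguity is that, at 33 per arm with r = 0.3 and SD 3.5, the same text supports either 66% or 80% power.

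These figures assume equal SDs at both visits, a true effect of 2.46, and that a single-visit SD from one arm of another study carries over to early RA.

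**What to change.** Make the primary analysis an ANCOVA of one-year aortic distensibility on treatment arm and baseline distensibility, and say so in the analysis paragraph. Baseline distensibility is already measured. Given a single-visit SD of at most 3.5 and the assumed effect, the stated 70%, 80% and 90% become approximate lower bounds and no longer depend on an unstated correlation. The sample-size paragraph should state that condition on the SD.

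If an unadjusted t-test on change is kept, name change as the analysed quantity, drop the description of 3.5 as conservative, and report power over a range of r, for example 0.3 to 0.7, or give an SD of change with its source.

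The cost is wording in two paragraphs, with no new patients or data. If change scores are kept, the restated power may be clearly less favourable at low r, for example 66% instead of 80% at 33 per arm with r = 0.3.
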